## Abstract

**Background:**

Many older adults rely on a manual wheelchair for mobility but typically receive little, if any, training on how to use their wheelchair effectively and independently. Standardized skill training is an effective intervention, but limited access to clinician trainers is a substantive barrier. *Enhancing Participation in the Community by Improving Wheelchair Skills* (EPIC Wheels) is a 1-month monitored home training program for improving mobility skills in older novice manual wheelchair users, integrating principles from andragogy and social cognitive theory. The purpose of this study is to determine whether feasibility indicators and primary clinical outcome measures of the EPIC Wheels program are sufficiently robust to justify conducting a subsequent multi-site randomized controlled trial.

**Methods:**

A 2 × 2 factorial randomized controlled trial at two sites will compare improvement in wheelchair mobility skills between an EPIC Wheels treatment group and a computer-game control group, with additional wheelchair use introduced as a second factor. A total of 40 community-dwelling manual wheelchair users at least 55 years old and living in two Canadian metropolitan cities (*n* = 20 × 2) will be recruited. Feasibility indicators related to study process, resources, management, and treatment issues will be collected during data collection and at the end of the study period, and evaluated against proposed criteria. Clinical outcome measures will be collected at baseline (pre-randomization) and post-intervention. The primary clinical outcome measure is wheelchair skill capacity, as determined by the Wheelchair Skills Test, version 4.1. Secondary clinical outcome measures include wheelchair skill safety, satisfaction with performance, wheelchair confidence, life-space mobility, divided-attention, and health-related quality of life.

**Discussion:**

The EPIC Wheels training program offers several innovative features. The convenient, portable, economical, and adaptable tablet-based, home program model for wheelchair skills training has great potential for clinical uptake and opportunity for future enhancements. Theory-driven design can foster learning and adherence for older adults. Establishing the feasibility of the study protocol and estimating effect size for the primary clinical outcome measure will be used to develop a multi-site randomized controlled trial to test the guiding hypotheses.

**Trial registration:**

Clinical Trials NCT01740635.

## Background

Canada has a rapidly growing aging population; over the next 50 years, the proportion of older people is expected to double to more than one in four [1]. With age, the risk of a disabling health condition increases; mobility is the most prevalent area of impairment among older adults in Canada [2]. The number of wheelchairs provided to address mobility issues among older adults is also rising. In 2001, an estimated 81,000 Canadians 65 years and older required a wheelchair for mobility [3] – a rate four times the national average. A 2004 study [4] reported that among multiple assistive device users, the manual wheelchair (MWC) was considered third most important, behind eyeglasses and canes. However, the wheelchair also represents a substantial cost to consumers and the health care system. Beyond the cost of purchase, which varies from several hundred to thousands of dollars, our clinical experience has demonstrated that the process of assessment, procurement, fitting, and delivery can reach $10,000 or more. These systemic costs are squandered if older adults are unable to use their wheelchair effectively to participate in important activities of life.

Merely acquiring a wheelchair does not guarantee independence or satisfactory performance with functional activities. In particular, environmental factors, such as carpet, ramps, curbs, gravel, and poor sidewalk conditions, present barriers to mobility and self-propulsion. In Canada, over 90% of older MWC users experienced restricted performance in at least one major life activity [2] (compared with 15% of those without a mobility device) and nearly 60% require assistance from a family member or other care provider for even basic mobility [3]. Restricted mobility is associated with reduced participation and a loss in social connectedness [5], which can lead to feelings of isolation, stress, and low self-esteem, impacting overall quality of life [6]. A 2006 study of stroke survivors adjusting to wheelchair use identified substantial restriction in caregivers’ social roles and an increased burden of care [7]. In Canada, 25% of caregivers of the elderly are over 65 years themselves [1], and risk both acute and overuse injury when assisting with wheelchair use [8].

In addition, MWC users are at risk of tips and falls, which often result in injury. In Canada, the yearly incidence of tips or falls is estimated to be 5.2%, with 4.2% resulting in injury and 2.5% requiring a visit to an emergency department [9]. In the United States in 2005, wheelchair-related accidents resulted in one death per week and treatment for a hospitalized injury was estimated at $25,000 to 75,000 [10].

Providing comprehensive skills training is effective, but relies on considerable 1:1 training time. The Wheelchair Skills Training Program [11] is the only structured training program reported in the literature. An expert clinician provides personal training, typically requiring four to eight sessions of an hour or more. Several studies have demonstrated the Wheelchair Skills Training Program to be safe and practical [12,13], and randomized controlled trials report a significant improvement in skill capacity among adult MWC users during inpatient rehabilitation [14] and in the community [15]. Improvements in safety with skill performance have also been reported [16]. While the evidence indicates such training is effective, there has not been widespread clinical adoption and as a result older adults receive little or no structured wheelchair skills training. Even among younger populations receiving inpatient rehabilitation, only 17 to 18% of wheelchair users receive any formal training [17,18], which typically focuses on such skills as transferring from the wheelchair to the bed, toilet, or bathtub. A survey of older veterans who were prescribed a wheelchair post-stroke found 53% had received no instruction at all on wheelchair use [19]. Another study of US veterans reported that more than 50% had difficulty with even basic wheelchair propulsion, despite having access to a trained clinician and a custom-fitted wheelchair [20].

Several factors contribute to the current situation of inadequate training. First, many clinicians do not have sufficient knowledge of (or ability to demonstrate) wheelchair skills [12]. Second, other competing demands are often prioritized over wheelchair training during in-hospital rehabilitation. Older adults are frequently discharged with a temporary (standard) wheelchair and delivery of a customized wheelchair occurs in community settings, when therapists’ time is limited. Finally, funding for home care and community-based services in Canada and the United States has been in decline and is insufficient to support clinician-intensive training either before or after discharge [21,22]. Often, the time and travel demands for both consumers and clinicians make traditional skills training cost-prohibitive [23]. Long wait lists and the inaccessibility of rehabilitation services, particularly in rural areas, further exacerbate the problem [23,24].

Delivering rehabilitation training as a monitored or self-managed home program among older adults has been effective for a variety of outcomes including strengthening [25], physical activity [26], self-care [21,27] and exercise [28,29]. Home programs are advantageous because they allow privacy for the user, occur in a familiar context, can be conveniently integrated into the user’s schedule, and do not require the time, effort, and expense of travel [26]. Adherence to any intervention is critical to its effectiveness. A 2010 Cochrane review of exercise interventions found those interventions that incorporated social cognitive theory (that is, self-efficacy), were monitored, and increasingly graded complexity of the activity were more effective in improving adherence, frequency, and duration of exercise [30].

Computer-related devices are becoming increasingly useful for rehabilitation interventions, with advances in affordability, size, portability, accessibility, and user-interface simplicity. Computer and popular gaming systems have shown promising results in rehabilitation by casting therapy in a more engaging and enjoyable context. Their use for physical activity training in rehabilitation among older adults has demonstrated high participation rates, increased motivation, and tolerance for activity, and trends toward improvement in fitness [31].

The Enhancing Participation in the Community by Improving Wheelchair Skills program (EPIC Wheels) is an individualized home training program that optimizes learning for older adults while limiting the time demands of expert trainers. The program content and delivery was developed using principles of andragogy (adult learning) [32,33] and social cognitive (self-efficacy) [34,35] theory. Using an affordable computer tablet device, EPIC Wheels provides a customized and mobile structured training program for in-chair or tabletop use at home and in the community. A touch-screen audiovisual display features interactive training and practice activities, and wireless Internet connectivity enables trainee-trainer communication and remote trainer monitoring. The EPIC Wheels program is 1 month long and includes a minimum of 10 hours of training and practice. Training includes two personalized sessions with a wheelchair expert; one at the outset and the second at the mid-point of the program.

Prior to moving to a large-scale randomized controlled trial (RCT), it is not only critical but also prudent to ensure that the feasibility indicators and the proposed clinical measures are sufficiently robust. This paper describes the objectives and design of the EPIC Wheels feasibility study that will be used to construct and implement a comprehensive, multi-site RCT trial that directly assesses the guiding hypotheses.

### Study objectives

#### Feasibility indicators

These have been selected to assess the feasibility of study methods and procedures, including:

• Process issues of subject recruitment, consent, retention, and perceived benefit.

• Resource issues of treatment adherence, burden of data collection, incorporating a health utility index, and intervention burden.

• Management issues of tablet reliability, subject processing, and protocol administration.

• Treatment issues of safety, response, and treatment effect.

#### Primary clinical outcome

The aim of the study is to evaluate the effect of EPIC Wheels on wheelchair skill capacity and obtain an estimate of the treatment effect size.

#### Secondary clinical outcome

The secondary aims are to evaluate the effect of EPIC Wheels on wheelchair skill safety, wheelchair use confidence, satisfaction with activity performance, mobility, divided-attention, and health-related quality of life.

## Methods/design

### Trial design

This study uses a two-site RCT to compare differences in older adults’ wheelchair mobility skills between an EPIC Wheels (treatment) group and a cognitive training (control) group, introducing 'extra wheeling’ as a second factor. A 2 × 2 factorial design randomly assigns subjects using a 1:1:1:1 allocation ratio between four groups: EPIC Wheels, EPIC Wheels with extra wheeling, cognitive training, and cognitive training with extra wheeling. To support balance between groups and masking of assignment, a central computerized randomization algorithm was designed by our statistician, with an undisclosed block size and stratified by site (*n* = 20 at each site). Once subjects are enrolled, a tester collects baseline data before a study coordinator contacts the statistician to obtain group assignment. A trainer will initiate contact with the subject and implement the 1-month program, after which time the tester will re-administer the outcome measures (see Figure 1). To address bias, subjects will be instructed not to discuss their program; separate trainers will be used for the treatment and control groups at each site; and testers will be blinded to group allocation. A protocol is included for control group trainers to identify the potential value of the control intervention for wheelchair mobility and strategies to prevent participant attrition.

**Figure 1 F1:**
[figure not shown]
Trial procedure.

### Ethics

The protocol for this study has been approved by the Research Ethics Boards at the University of British Columbia (Approval number, H12-02043) and the University of Manitoba (Approval number, HS15818), as well as the research review committee of the regional health authority for each site. All study subjects, and their caregivers, will provide informed consent prior to enrolment. The study was funded through a peer-reviewed operating grant from the Canadian Institutes of Health Research (MOP-123240).

### Participants

A total of 40 community-dwelling MWC users living in two Canadian cities (20 at each site) will be recruited on a voluntary basis. Each site will have 20 participants, with five participants in each of four groups: treatment with extra wheeling, treatment without extra wheeling, control with extra wheeling, and control without extra wheeling. To optimize the impact of the treatment, individuals with less than one year of MWC use will be recruited. Novice users are still developing routines and patterns of wheelchair use and are potentially more amenable to adapting their mobility techniques [12]. Subjects will be ≥55 years old; live in the community within the metropolitan boundaries; self-propel a MWC ≥1 hour/day; use their MWC for mobility inside and outside their home; have used a MWC for <1 year; and have a caregiver willing to attend training sessions and supervise home training. There are no specific diagnostic criteria for enrolment; however, subjects must be able to propel a wheelchair with both hands. Individuals will be excluded if they cannot communicate and complete study questionnaires in English; anticipate a health condition or procedure that contraindicates training (for example, surgery scheduled which would impair physical activity); or are currently receiving outpatient therapy that includes wheelchair mobility training. A caregiver for each participant will also provide consent to participate in the study, and both subject and caregiver will indicate whether they are willing to be contacted for follow-up after the study is complete.

### Sample size

To address the feasibility indicators, the number of subjects is large enough to represent the target population and assess the feasibility criteria [36]. In addition, the sample size is powered to detect a statistically significant difference between groups and provide a reasonable estimate of a treatment effect. With a 2 × 2 factorial design, sample size can be calculating using each main factor independently, and then determined by selecting the larger of the two estimates [37]. Our calculations are based on the primary clinical outcome measure (the Wheelchair Skills Test version 4.1, WST), as this will be used in subsequent EPIC Wheels studies. Research in the field of wheelchair skills training is still maturing, with three published studies using actual users, and given the novel home program approach an α of 0.10 was selected to ensure a potentially beneficial treatment effect would not go undetected (Type I error rate). Given the absence of data regarding the impact of extra wheeling, we opted to use a comparable effect size (*f* = 0.54) in the second factor calculation. To minimize the risk of identifying such an effect merely by chance (Type II error), the study is powered at 90%. Based on a sample size calculation for analysis of covariance (ANCOVA) each of the four groups would require eight subjects for a total of 32 participants. In previous Canadian trials, a 9 to 18% dropout rate has been reported; conservatively adjusting for a 25% dropout rate (32/0.75), a total study *N* of 44 is planned (*n* = 11 for each group).

Previously published studies have used younger or mixed age populations; data specific to older adults are not available. We obtained permission to use a data subset (adults >50 years) from a yet-to-be published study ([name], personal communication) that provided WST change scores following training and powered our study to capture a comparable change (*m* = 9.3%; *s* = 9.5%). A difference of 9.3% corresponds to an acquisition of three additional skills on the WST; previous studies report that subjects perceive a clinically important difference with such improvements [17,18]. In fact, the skills performed on the WST are sequenced from simple (for example, rolling forwards) to moderate (for example, propelling on carpet) to complex (for example, ascending a 10° ramp). Research literature reporting on MWC use among older adults specifically implicates carpet, inclines, curbs, gravel, and poor sidewalk conditions as barriers to independent mobility [7]. Acquisition of even one of these important skills could quite reasonably represent a minimally clinically important difference (MCID) to wheelchair users, their caregivers, and those providing training. No formal MCID has been established for the WST; however, using data from a Canadian trial [18], a smallest detectable difference calculation suggests that a difference of 9.2% would exceed any measurement error or noise [38]. A reliability change index calculation indicates that 3.0% is the minimal detectable change required and is a reasonable proxy for MCID [38].

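### The planned total is 40 in three places and 44 in the sample-size section, and 40 does not deliver the stated 25% dropout allowance

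*Protocol article*

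**What the plan says.** Three places in the protocol article give a total of 40.

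- Abstract, Methods: "A total of 40 community-dwelling manual wheelchair users at least 55 years old and living in two Canadian metropolitan cities".
- Methods/design, Trial design: allocation is 1:1:1:1 over four groups and is "stratified by site (*n* = 20 at each site". With two sites this makes 40.
- Methods/design, Participants: "A total of 40 community-dwelling MWC users living in two Canadian cities (20 at each site) will be recruited". The same section gives the layout: "Each site will have 20 participants, with five participants in each of four groups". That is 10 per group over the two sites.

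The Sample size section ends elsewhere. It derives eight evaluable participants per group, 32 in all, for 90% power at α = 0.10. It cites dropout of 9 to 18% in earlier Canadian trials, allows for 25%, and concludes: "conservatively adjusting for a 25% dropout rate (32/0.75), a total study *N* of 44 is planned (*n* = 11 for each group".

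No section explains why the two totals differ.

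**The concern.** Both totals are stated as the plan, and they cannot both be right: 10 per group or 11 per group, 20 per site or a larger number at one or both sites. They also cannot be read as two stages of one flow, such as 44 enrolled and 40 completing. The Participants section gives 40 as the number to be recruited, and the Sample size section gives the evaluable number as 32.

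Two things are at stake. First, the dropout protection described in the Sample size section belongs to 44. A reader who takes 40 as the target would wrongly think it allows for 25% dropout. Second, this is a feasibility study in which recruitment and retention at each site are named process indicators (Data collection), and dropout findings are meant to inform later sample-size calculations. An ambiguous target makes recruitment harder to judge: 40 enrolled is 100% of one target and 40/44 = 91% of the other. The Trial status section says recruitment is already under way, so the figure should be settled before the lower target is reached.

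**Working it through.** **Inputs, all from the protocol article**

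- Sample size section: f = 0.54, α = 0.10, power 90%, 32 evaluable (8 per group), dropout allowance 25% applied by division, earlier dropout 9 to 18%.
- Trial design section: four groups, equal allocation.
- Statistical analyses section: ANCOVA with baseline score as the one covariate.
- Assumption: f = 0.54 applies to both main effects. The article prints it when describing the second factor and calls it comparable to the first.

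**Step 1. Reproduce the 32.** Power of a main-effect F test with 1 numerator df, N − 5 denominator df (four cells, one covariate) and noncentrality f² × N, where f² = 0.54² = 0.2916:

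| Evaluable N | Noncentrality | Power |
|---|---|---|
| 30 | 8.75 | 0.891 |
| 32 | 9.33 | 0.909 |
| 33 | 9.62 | 0.916 |

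The smallest N that reaches 0.90 is 31. Rounded up to four equal groups this is 32, so the stated figure reproduces.

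**Step 2. Reproduce the 44.** 32/0.75 = 42.67, which is 43 in total. Done per group, 8/0.75 = 10.67, rounded up to 11, and 4 × 11 = 44. The stated figure reproduces.

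**Step 3. Try to reproduce the 40.** Dividing by 0.75 gives 43 or 44, not 40. Multiplying instead, 32 × 1.25 = 40 exactly. That might be where the 40 came from, but the article does not say so.

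**Step 4. Completers under each total**

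| Dropout | From 40 | From 44 |
|---|---|---|
| 9% | 36.4 | 40.0 |
| 18% | 32.8 | 36.1 |
| 20% | 32.0 | 35.2 |
| 25% | 30.0 | 33.0 |

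The largest dropout at which 40 still yields 32 completers is 1 − 32/40 = 20%. At the plan's own 25%, 40 falls two short (30 against 32) and 44 does not (33).

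**The case against.** The strongest reply is that little depends on it. The shortfall is two completers against the rounded 32, or one against the unrounded minimum of 31. Power moves from a stated 90% to about 89%. The article itself calls the 25% conservative, and across the 9 to 18% it cites, 40 leaves enough completers. The main purpose is feasibility. All of this stands, and it limits the severity. It does not remove the contradiction: a plan needs one planned total, and its dropout statement must match it.

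A reader might infer more than the article supports, in three ways.

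- *That the randomisation lists, or a recruitment stop, are set at 40.* The Trial design section describes a central computerised algorithm with an undisclosed block size and a planned 20 per site. It describes neither a list length nor a stopping rule.
- *That the 90% power was derived for 44.* It was derived for 32 evaluable participants. Only the dropout inflation leads to 44.
- *That 44 cannot be balanced over two sites.* An even split is 22 per site, or 5.5 per cell, but the article does not say that 44 would be split evenly. Sites of 24 and 20 give 6 + 5 = 11 in every group. At 22 and 22, cells of five and six can also total 11 per group, and the Statistical analyses section provides for unequal cells. What holds is narrower: 44 conflicts with the stated 20 per site and five per cell.

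It is also fair to say that the article does not prove which total is operative. Three sections and the cell layout point to 40, while the formal calculation points to 44.

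**Conclusion.** The plan is wrong as written, with moderate severity. The defect is an inconsistency between sections. The sample-size arithmetic is sound within its own section, since both 32 and 44 reproduce. What fails is the link to the other three sections: 40 does not carry the 25% allowance and supports at most 20% if 32 completers are to remain.

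Under the plan's own 25% the cost is two completers and power of about 0.891, roughly one point below the stated 90%. At 20% dropout or less there is no shortfall against 32. This rests on f = 0.54, α = 0.10, one numerator df, four cells and one covariate, a set of assumptions that reproduces the stated 32. The result does not support a claim that the trial is materially underpowered at 40.

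**What to change.** The sponsor should confirm which total is operative, state it in every section, and give the dropout allowance that belongs to it.

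- **If it is 40**, as three sections and the five-per-cell layout indicate, replace the sentence on 25% and 44 in the Sample size section with: *A total of 40 (10 per group) allows 20% attrition (32 completers), above the 9 to 18% previously reported; at 25% attrition 30 remain and power is about 89%.* This changes one sentence and adds no participants. The price is a smaller stated allowance. The Discussion warns that control participants may be more likely to drop out, so the 20% should be given openly as the limit.
- **If it is 44**, keep the Sample size section and correct the total, the 20 per site and the five per cell in the abstract, Trial design and Participants sections, stating how 44 is divided between the sites. Relative to 40 this means four more participants.

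Either way, any recruitment criterion that is expressed against the planned total should use the confirmed figure.
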